### Further research questions

#### Duration

To investigate whether a prolonged intake facilitates increased symptom improvements, linear mixed models which align with the ones of the efficacy question are performed to examine differences between the groups OLP 4wk and OLP 8wk. With *n* = 25 participants per group, significant effects would be present if the effect size was Cohen’s *d* = 0.8. Since no study has investigated the duration of OLP in a randomized-controlled design, we are unaware of whether an effect exists at all. Hence, the comparison between the two OLP groups is exploratory and the study not deliberately powered for this sub-analysis.

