It has long been viewed that placebos cannot be administered in accordance with ethical values since deception would be necessary for the occurrence of beneficial effects. This notion has been shaken up by studies on open-label placebos (OLP) showing that placebos can lead to positive effects even though their inert nature *is* disclosed [28–35]. The first randomized-controlled OLP trial demonstrated a significant improvement of irritable bowel syndrome after 3 weeks of placebo intake over an untreated control group with 60% (vs 35%) reporting adequate relief [30]. Clinical trials have since been conducted among patients with chronic low back pain [28], cancer-related fatigue [36], as well as smaller ones on depression [31] and allergic rhinitis [32, 33], with reporting of medium to large effect sizes. Experimental studies with healthy cohorts have also been conducted [29, 34, 35]. Up to now, the number of trials is small and underlying mechanisms are unclear.

The objective of this study is to determine whether OLP is efficacious to treat hot flushes. Further, we will analyze the response rate of OLP and health-related quality of life, whether beneficial effects can be maintained or increased with a prolonged placebo treatment, and whether beneficial effects are related to positive expectations.

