## Methods/design

### Study design

In this randomized-controlled, assessor-blinded superiority trial, menopausal women with hot flushes are assigned 1:1 to a 4-week OLP treatment or a no-treatment control group. The control group allows for examining whether OLP has beneficial effects over and above spontaneous improvement and statistical phenomena. Patients receive three study visits at enrolment, baseline, and post-treatment (Fig. 1). Women allocated to OLP are randomized a second time at post-treatment to either another 4 weeks of placebo (OLP 8wk) or to discontinue the treatment (OLP 4wk). Accordingly, OLP 8wk and OLP 4wk receive a fourth study visit at 8 weeks follow-up, whereas, for the no-treatment group, the study ends at week 4. Two calls at weeks 2 and 6 are conducted to inquire about adverse events and adherence. To further understand the experiences of participants and potential psychological mechanisms from their perspective, qualitative interviews will be conducted with a subgroup of patients who have reported improvements under the placebo. Ethics approval is given by the Physicians’ Chamber of Hamburg (reference number PV5787). The trial is registered at ClinicalTrials.gov (ID NCT03838523) and complies with the SPIRIT guidelines [37].

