#### Maintenance

To test whether beneficial effects can be sustained after the intake is stopped, we perform contrast analyses within the OLP 4wk group with the pre-defined contrasts (A) ‘baseline’ vs ‘4 wk’, (B) ‘baseline vs ‘8 wk’, and (C) ‘4 wk’ vs ‘8 wk’. If sustained efficacy is given, contrasts (A) and (B) would be statistically significant, whereas contrast (C) would be non-significant. Aligned with the “duration” question, this question is also an exploratory one.

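### The exploratory Duration comparison (OLP 8wk versus OLP 4wk) estimates continuing versus stopping, so alone it cannot tell increased benefit from maintained benefit

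*Protocol article*

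**What the plan says.** All references are to the protocol article.

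- **Background** lists among the aims "whether beneficial effects can be maintained or increased with a prolonged placebo treatment". Maintaining and increasing are thus named as two possible results of longer treatment.
- **Study design** re-randomises the OLP group at week 4: OLP 8wk takes placebo for four more weeks and OLP 4wk stops. It also says that "for the no-treatment group, the study ends at week 4".
- **Duration** gives its aim as "To investigate whether a prolonged intake facilitates increased symptom improvements". Linear mixed models patterned on the efficacy models "are performed to examine differences between the groups OLP 4wk and OLP 8wk". It counts on 25 women per group and d = 0.8, and it calls the comparison exploratory and not deliberately powered.
- **Maintenance** says "we perform contrast analyses within the OLP 4wk group with the pre-defined contrasts" of baseline, week 4 and week 8. Sustained efficacy is read from (A) and (B) being significant, "whereas contrast (C) would be non-significant". (C) compares week 4 with week 8. No corresponding contrast is named for OLP 8wk.

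**The concern.** The question is whether longer intake adds improvement. That is a statement about what happens in OLP 8wk after week 4. The comparison assigned to it also contains whatever happens in OLP 4wk after placebo is withdrawn. A week-8 advantage for OLP 8wk could mean that continued intake brought more relief, that it only held the week-4 level while the other group lost ground, or a mixture of the two.

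The Background section treats the first two as different answers. The Relevance section says that the duration and maintenance questions bear directly on possible clinical uses of OLP. Whether longer intake adds benefit or only prevents its loss is a distinction the trial should be able to report, and the named comparison does not supply it.

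**Working it through.** **Step 1: what the comparison estimates.** Randomisation makes the two groups equal on average at week 4. With lower scores better:

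week-8 difference (OLP 4wk − OLP 8wk) = (rise in OLP 4wk after week 4) + (further fall in OLP 8wk after week 4)

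Only the sum is estimated. The stated aim concerns the second term.

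**Step 2: the plan's own figure.** Inputs from Duration and Statistical analyses: 25 per group, d = 0.8, two-sided α = 0.05. Noncentrality = 0.8 × √(25/2) = 2.83 on 48 df, giving power 0.79 by the t-test (0.81 by the normal approximation). The section states no power; if the 80% of the Power analysis section is meant, the figure reproduces. With 10% attrition (22 to 23 per group), power is 0.74 to 0.76.

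**Step 3: response to relapse and to gain.** SD 10 is from the Power analysis section. Assumptions: the sizes of relapse and gain, a week-4/week-8 correlation r of 0.5 to 0.7, equal week-4 means, and a t-test on week-8 scores in place of the mixed model. Results for 25 per group (20,000 simulated trials per scenario):

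| Change after week 4 (OLP 4wk / OLP 8wk) | Duration significant | Week 4 vs week 8 within OLP 8wk significant |
|---|---|---|
| +8 / 0 (relapse only) | 79% | 5% |
| 0 / −8 (gain only) | 79% | 97% to >99% |
| +4 / −4 (mixed) | 79% | 48% to 70% |
| +6 / 0 | 55% | 5% |
| 0 / −6 | 55% | 82% to 96% |
| +4 / 0 | 28% | 5% |
| 0 / −4 | 28% | 49% to 70% |

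The Duration column depends only on the sum. The last column separates the cases.

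**Step 4: how far contrast (C) helps.** (C) is a paired test in OLP 4wk. The SD of the change is 10 × √(2(1 − r)): 10.0 at r = 0.5 and 7.75 at r = 0.7. For a 4-point relapse the noncentrality is 4√n / SD:

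- n = 25, r = 0.7: 4 × 5 / 7.75 = 2.58, power about 0.70, missed about 30%.
- n = 25, r = 0.5: 4 × 5 / 10 = 2.00, power about 0.48, missed about 52%.
- n = 22, r = 0.5: 4 × 4.69 / 10 = 1.88, power about 0.43, missed about 57%.

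For an 8-point relapse at 25 per group, (C) is significant in 97% of trials or more.

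**Step 5: both results together under relapse only.** The share of all trials with Duration significant and (C) non-significant, for 22 to 25 per group and r = 0.5 to 0.7, is:

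- 4-point relapse: about 6% to 10%, or roughly 20% to 40% of the significant Duration results
- 6-point relapse: about 1% to 8%
- 8-point relapse: under 3%

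These joint figures are for a test on week-8 scores alone. A model that also used week-4 scores would give lower ones.

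**The case against.** The case on the other side is substantial.

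- **No decision rule is printed.** A reader might infer that the plan would report a relapse as added benefit in about half of trials, since a pure 6-point relapse makes Duration significant about 50% to 55% of the time with 22 to 25 per group. The article does not support that. Duration states an aim and a comparison but no rule for reading the result; only Maintenance gives one. The figure also ignores (C), which sits in the next section and would usually be significant as well.
- **The randomised comparison is valid.** It answers whether eight weeks of intake leaves women better off at week 8 than four weeks. This stands, and the comparison should be kept.
- **The absent untreated arm does not bias it.** A reader might infer that ending the no-treatment group at week 4 undermines the Duration comparison. It does not, because natural course acts on both randomised OLP groups alike. It limits only a within-group reading of OLP 8wk.
- **The separating contrast can be estimated from the planned model.** The efficacy models include group, measurement point and their interaction, and a condensed article may leave extra contrasts to a fuller document. This shows how cheap the repair is. But the article does state an aim and assign a comparison to it, and the two do not match. It also lists time contrasts for OLP 4wk alone.
- **The analysis is exploratory.** True, and this keeps the point minor.

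Two things remain. Duration does not link its reading to (C), and (C), being confined to OLP 4wk, cannot show further gain in OLP 8wk.

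**Conclusion.** The point holds as a mismatch between a stated exploratory aim and the comparison assigned to it. Taken alone, OLP 8wk versus OLP 4wk cannot distinguish increased from maintained benefit; this follows from the design and needs no assumption.

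The practical risk is limited. Read beside (C), a large relapse would seldom go unnoticed. For a relapse of about 4 points, (C) misses some 30% to 57%, and in about 6% to 10% of trials the two results together could suggest sustained effect plus added gain when there was relapse only. Those figures rest on SD 10 from the article and on the assumed relapse size, correlation, 22 to 25 women per group and simple t-tests.

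Severity is minor. The primary outcomes, the sample size and the main conclusion are untouched.

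**What to change.** In the Duration section:

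1. Describe the OLP 8wk versus OLP 4wk difference at week 8 as the randomised effect of continuing versus stopping.
2. Add the week-4 versus week-8 contrast within OLP 8wk, with its 95% CI, and report it beside contrast (C). The interval matters because the groups are small: a 4-point change would reach significance only about half to 70% of the time with 25 women, so a non-significant result would not show absence of gain.
3. Speak of increased improvement only if OLP 8wk itself improves after week 4, and note that this within-group change has no untreated control after week 4. Otherwise report only whether continuing was better than stopping.

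The cost is one more contrast from the model already planned and a few changed sentences. No new data are needed. The price is a more modest claim about duration.

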#### Maintenance

To test whether beneficial effects can be sustained after the intake is stopped, we perform contrast analyses within the OLP 4wk group with the pre-defined contrasts (A) ‘baseline’ vs ‘4 wk’, (B) ‘baseline vs ‘8 wk’, and (C) ‘4 wk’ vs ‘8 wk’. If sustained efficacy is given, contrasts (A) and (B) would be statistically significant, whereas contrast (C) would be non-significant. Aligned with the “duration” question, this question is also an exploratory one.

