### Power analysis

The power calculation is based on our primary outcome hot flush score. The software G*Power was used to calculate the sample size a priori [42]. Since no OLP study has been conducted in the field of hot flushes, we base our sample size calculation on two separate clusters of information. From double-blind hot flush trials we can expect a moderate effect size of Cohen’s *d* = 0.40 given a mean of 19, standard deviations of 10 [23], and a four-point reduction in the hot flush score (frequency × severity) after 4 weeks of placebo [43]. Based on previous OLP trials in patients with irritable bowel syndrome and chronic low back pain, a large effect size of *d* = 0.80 can be expected [28, 30]. Combining these two clusters of information, a moderate to large effect size is expected for the difference between the OLP and the no-treatment groups at post-treatment. For a two-tailed Student’s *t*-test with an *α*-error rate of 0.05, a number of *N* = 90 participants would provide an 80% power to detect an effect of *d* = 0.60. We assumed an attrition rate of 10% and obtained our required sample size of *n* = 100 women.

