### SV 2: Baseline—allocation

At the second study visit, patients are informed about their assignment by a clinician. Clinicians are not aware of the group assignment until the patient has opened the envelope and disclosed the allocation result. Clinicians instruct the OLP group to take two pills a day for 4 weeks, each morning and evening after a meal. A total number of 56 pills are handed out in paper packaging which includes the pill bottle and the original medication leaflet of the producing company. The bottle shows the name of the pill (“placebo”), the number of pills and its equivalent in grams, a subtitle (“for menopausal hot flushes”), the contact data of the responsible party (“Department of Psychosomatic Medicine and Psychotherapy”) and further instructions regarding the pills (e.g. “Store inaccessible to children”). Women are reminded about the importance of taking the pills faithfully and a 50% chance of continuing the treatment for another 4 weeks. Women assigned to the no-treatment group are reminded of the meaning of this study group. The duration of the second study visit is 5 to 10 min.

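### The exploratory maintenance contrasts use only the OLP 4wk half for the baseline and week-4 means, which is unbiased but gives away precision that the design supplies at no cost

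*Protocol article*

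**What the plan says.** The Maintenance section asks whether benefit persists once the pills are stopped. Its method is that "we perform contrast analyses within the OLP 4wk group with the pre-defined contrasts" (A) baseline vs week 4, (B) baseline vs week 8 and (C) week 4 vs week 8. If efficacy is sustained, "contrasts (A) and (B) would be statistically significant, whereas contrast (C) would be non-significant". The section adds that "this question is also an exploratory one".

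Four other parts of the protocol article bear on this:

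- **SV 2 (Baseline—allocation):** there is one regimen for the whole arm. "Clinicians instruct the OLP group to take two pills a day for 4 weeks", and every OLP woman is told that she has an even chance of continuing.
- **Study design:** "Women allocated to OLP are randomized a second time at post-treatment".
- **SV 3 and Randomization:** the clinician first asks about hot flushes and then discloses the second allocation, which is 1:1 in permuted blocks stratified by perceived improvement (yes/no).
- **Duration:** the two OLP subgroups are compared "With *n* = 25 participants per group".

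**The concern.** Until the third visit there is a single OLP group, with the same pills, visits, call and diary. The women who will later stop are a random half of it. Contrast (A) uses nothing recorded after the split, so restricting it to that half leaves out half of the relevant observations and gains no validity. Contrasts (B) and (C) each have one end before the split, and that end could also be estimated more precisely.

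What is at stake is limited but real. The section judges sustained efficacy by a pattern of significant and non-significant contrasts, and significance of (A) is part of that pattern. An analysis in a subgroup this small, which the trial was not sized for, has little reason to set aside valid data.

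**Working it through.** **The plan's own figures.** Two-sided two-sample t-tests at 0.05:

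- Power analysis: 45 per group (N = 90) and d = 0.60 give 80.4% power against the stated 80%; 90 / 0.9 = 100.
- Duration: 25 per group and d = 0.8 give 79.1%. The section states no power level; this is close to 80%.

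Both reproduce. The maintenance contrasts have no stated figure.

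**Inputs.**

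- n = 25 in each OLP subgroup, 50 in all (Duration). With the 10% attrition of the Power analysis section, 45 in all, so 22 or 23 per subgroup.
- SD 10 and "a four-point reduction in the hot flush score (frequency × severity) after 4 weeks of placebo" (Power analysis). The adopted d = 0.60 corresponds to 0.60 × 10 = 6 points. That is a between-group difference; using it as a within-arm fall is an assumption.
- The correlation ρ between time points is not given. It is varied.
- Three time points (weeks 0, 4, 8), a simplification of the weekly means. Stratification of the second randomization is ignored.

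**Contrast (A).** Var(A) = 2σ²(1 − ρ)/n. Going from n = 25 to n = 50 halves it at every ρ. The SE ratio is √0.5 = 0.707, a fall of 29%; the planned SE is 1/0.707 = 1.41 times the attainable one. At ρ = 0.5 the SE goes from 2.00 to 1.41 points.

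**Contrasts (B) and (C).** The baseline and week-4 means are shared across all OLP women. The OLP 4wk week-8 mean is adjusted by regression on the earlier time points. The variance ratio, joint model to OLP 4wk alone (25 + 25 women), is:

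| Structure | (B) | (C) |
|---|---|---|
| Compound symmetry | (3 + 4ρ)/(4(1 + ρ)) | same |
| AR(1), ρ per 4 weeks | 0.75 | (3 + ρ)/4 |

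Taking square roots:

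| Setting | SE ratio (B) | SE ratio (C) |
|---|---|---|
| Compound symmetry, ρ = 0.3 | 0.899 | 0.899 |
| Compound symmetry, ρ = 0.6 | 0.919 | 0.919 |
| Compound symmetry, ρ = 0.9 | 0.932 | 0.932 |
| AR(1), ρ = 0.5 | 0.866 | 0.935 |
| AR(1), ρ = 0.7 | 0.866 | 0.962 |
| AR(1), ρ = 0.8 | 0.866 | 0.975 |

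So the SE of (B) falls by about 7–13% and that of (C) by about 2.5–10%. The Efficacy section's model has a random intercept plus an autoregressive residual, which lies between the two structures.

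**Power for (A).** Paired t-test, SD of change = 10√(2(1 − ρ)). At ρ = 0.6 this is 8.94.

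| True fall | n = 22 | n = 25 | n = 45 | n = 50 |
|---|---|---|---|---|
| 4 points | 52% | 57% | 84% | 87% |
| 6 points | 85% | 90% | >99% | >99% |

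For a 4-point fall at other correlations, 25 women against 50: 48% against 79% (ρ = 0.5), 70% against 95% (ρ = 0.7), 86% against 99% (ρ = 0.8).

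**The case against.** The planned analysis is legitimate. Following the women who stop through baseline, week 4 and week 8 is a natural and unbiased way to ask about maintenance. The section calls the question exploratory, and the Duration section says the study was not deliberately powered to compare the two OLP subgroups. All of that stands, and it sets the severity.

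A reader might infer that a non-significant (A) would lead the trial to report that there was no benefit to sustain. The document does not support that. Week-4 benefit is judged by the primary analysis in the Efficacy section, which compares the intent-to-treat OLP group with no treatment. The OLP 8wk women's early data are absent only from these contrasts. The Maintenance section also describes the pattern expected under sustained efficacy; it does not say that failure of (A) means no benefit.

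A reader might also infer that (A) is bound to be badly underpowered. That depends on the input. The 4-point fall is only one of the two sources in the Power analysis section; at 6 points and a correlation of 0.6 the planned power is already 85–90%.

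The contrast closest to the maintenance question, (C), gains least, because week 8 off treatment is observed only in OLP 4wk. This is correct and limits the benefit.

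Finally, the contrasts might come from the joint duration model, since the article does not name the fitted model. But with a full group-by-time interaction (A) would still rest on OLP 4wk alone. The pre-split means have to be shared explicitly, and confining the contrasts to that group makes this unlikely.

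**Conclusion.** The point holds as a loss of efficiency in an exploratory analysis, not as an error or a bias. The 29% reduction in the SE of (A) rests on equal halves and common pre-split means, and does not depend on the correlation. The smaller gains for (B) and (C), and every power figure, rest on assumed correlations. No primary or secondary conclusion changes; what improves is the reliability of the significance pattern used to judge sustained efficacy. Lowest severity: a free improvement.

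**What to change.** Fit one mixed model to all OLP women, with common means up to week 4 and separate OLP 4wk and OLP 8wk means for weeks 5–8. Account in the model for the perceived-improvement stratum, since the second randomization was stratified on it. Estimate (A) from all OLP women, and (B) and (C) for OLP 4wk from the same model; B = A + C still holds by construction.

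The cost is a sentence or two of analysis wording and no new data. The one visible change is that (A) no longer describes only the women who stop, which is harmless because they are a random half of the arm. The contrasts within OLP 4wk alone can be shown alongside.

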### Statistical analyses

All hypotheses are tested two-sided with an *α*-level of 0.05.

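### The exploratory maintenance analysis counts a non-significant week-4 versus week-8 contrast, alongside two uncontrolled before-after contrasts, as sustained efficacy; with about 22–25 women that pattern cannot show it

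*Protocol article*

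**What the plan says.** The Maintenance section of the protocol article says of its method: "we perform contrast analyses within the OLP 4wk group with the pre-defined contrasts" (A) baseline versus week 4, (B) baseline versus week 8 and (C) week 4 versus week 8. It then states the pattern that goes with maintenance: "If sustained efficacy is given, contrasts (A) and (B) would be statistically significant, whereas contrast (C) would be non-significant". It names no margin, no fraction of the benefit that must be retained, and no confidence-interval criterion. It adds: "Aligned with the “duration” question, this question is also an exploratory one".

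The Study design section explains why there is an untreated arm: "The control group allows for examining whether OLP has beneficial effects over and above spontaneous improvement and statistical phenomena". It also says that "for the no-treatment group, the study ends at week 4".

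The Duration section plans a mixed-model comparison of OLP 4wk with OLP 8wk, gives 25 women per subgroup, and says that the trial was not powered for it. The Maintenance section does not draw on that randomised comparison.

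**The concern.** The pattern has two weaknesses, which act together.

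- **Contrast (C).** Failing to reject no change is treated as part of the evidence for no change. With one small arm, (C) can easily be non-significant while much of the benefit has gone.
- **Contrasts (A) and (B).** These are changes from baseline in women admitted because their flushes were frequent and bothersome. Natural course and regression to the mean push such changes towards improvement. The Background section itself leaves open whether improvement on placebo exceeds these. The control group exists to remove them, but (A) does not use it, and by week 8 there is none for (B) or (C).

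At stake is a statement that the effect outlasts the treatment. The Relevance section says the duration and maintenance questions matter particularly for possible clinical uses of OLP.

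**Working it through.** **Inputs from the protocol article**
- SD 10 for the hot flush score, and a planning effect of d = 0.60 (Power analysis). The benefit is therefore 0.60 × 10 = 6 points.
- 25 women per OLP subgroup (Duration). With 10% attrition (Power analysis), 25 × 0.9 = 22.5, so about 22.
- Two-sided α of 0.05 (Statistical analyses).

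**Assumptions not in the document**
- Within-woman correlation r of 0.5, 0.7 or 0.8, equal between all pairs of time points.
- Natural improvement of 0, 2, 4 or 6 points, present at both week 4 and week 8.
- A paired t-test stands in for the planned mixed-model contrast. Extra weekly data could add some precision.

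**The plan's own figure.** The Duration section says that with n = 25 "participants per group, significant effects would be present if the effect size was Cohen’s" d = 0.8. A two-sample t-test with 25 per arm at d = 0.8 has 79.1% power, so the figure reproduces if 80% power was meant. It concerns the comparison between the two OLP arms, not contrast (C).

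**Step 1: contrast (C) alone, 3 of 6 points lost.** The SD of the change is 10·√(2(1−r)), the standard error is that divided by √n, and the non-centrality is 3 divided by the standard error. P(non-significant) comes from the non-central t distribution.

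| r | SD of change | Non-centrality, n = 25 / 22 | (C) non-significant, n = 25 / 22 | 95% CI half-width, n = 25 / 22 |
|---|---|---|---|---|
| 0.5 | 10.0 | 1.50 / 1.41 | 70% / 73% | 4.1 / 4.4 points |
| 0.7 | 7.75 | 1.94 / 1.82 | 54% / 59% | 3.2 / 3.4 points |
| 0.8 | 6.32 | 2.37 / 2.22 | 38% / 44% | 2.6 / 2.8 points |

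At r = 0.5 or 0.7 the interval around an observed change of zero still includes a 3-point loss.

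**Step 2: the full pattern, 3 of 6 points lost.** (B) must also be significant. With no natural improvement, (B) rests on the 3 points that remain. By symmetry its power is 100% minus the step 1 figures: 27–30% at r = 0.5, 41–46% at 0.7 and 56–62% at 0.8. I simulated three correlated normal time points (200,000 trials per cell) and counted trials with (A) and (B) significant for improvement and (C) non-significant.

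| Natural improvement | r = 0.5, n = 25 / 22 | r = 0.7, n = 25 / 22 | r = 0.8, n = 25 / 22 |
|---|---|---|---|
| 0 points | 25% / 22% | 32% / 30% | 30% / 31% |
| 2 points | 52% / 49% | 51% / 53% | 37% / 43% |
| 4 points | 67% / 67% | 54% / 58% | 38% / 44% |

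Once natural improvement makes (A) and (B) nearly always significant, the rate is set by (C) and approaches the step 1 figures.

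**Step 3: no OLP effect at all.** The same natural improvement is present at weeks 4 and 8, with nothing gained and nothing lost.

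| Natural improvement | Full pattern met (r 0.5–0.8, n 22–25) |
|---|---|
| 2 points | 5–17% |
| 4 points | 26–74% |
| 6 points | 62–94% |

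**The case against.** **The analysis is exploratory.** The protocol says so, and no primary or secondary conclusion depends on it. That stands and lowers the severity. It excuses low power, but not reading low power as a positive finding.

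**All three conditions must hold.** A reader might infer from step 1 that a half loss would usually be called maintenance. The documents do not support that. (B) must also be significant, and with no natural improvement the full pattern is met in only about 22–32% of trials. If 4 of the 6 points were lost it would be about 9–13%. It becomes the more likely verdict only with added natural improvement and moderate correlation, and the protocol gives a figure for neither. At r = 0.8 the half loss stays below 50% even for (C) alone.

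**Smaller samples do not always favour the pattern.** They make (C) easier to satisfy but (A) and (B) harder, so it would be wrong to say that less data always helps the maintenance conclusion.

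**The randomised comparison is already planned.** True: the Duration section has it. It is used there to ask whether longer intake adds benefit and is not brought to bear on maintenance.

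**The sentence gives an expectation, not a rule.** Literally, it says what would be seen if efficacy were sustained. But the section introduces the contrasts as the test of that question and offers no other criterion, so the pattern is what an analyst would apply.

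**Conclusion.** The point holds in a limited form. As written, the maintenance pattern cannot show that benefit is sustained, because a non-significant (C) in 22–25 women is compatible with losing half the planned benefit (38–73% of trials over r of 0.5 to 0.8), and because (A) and (B) cannot separate an OLP effect from natural course.

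The chance that the full pattern mislabels a half loss is about 22–32% without natural improvement and about 38–67% with 4 points of it. The weakness that matters more is that the pattern can be met by a treatment that did nothing: about 26–74% of trials with 4 points of natural improvement and 62–94% with 6. These figures rest on SD 10, the 6-point benefit, the assumed correlations and the paired-t approximation, and they apply to the hot flush score only.

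The text should be changed, but severity is modest because the question is exploratory.

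**What to change.** 1. Drop non-significance of (C) as a criterion. Report the OLP 4wk change from week 4 to week 8 with its 95% confidence interval. State a margin in advance, and call the effect sustained only if the interval excludes a loss larger than that margin.
2. Use the planned randomised OLP 4wk versus OLP 8wk comparison, at week 8 and adjusted for the week-4 score and the second-randomisation stratum (perceived improvement), as the controlled estimate of the effect of stopping. Report it with its interval, and do not read a non-significant difference there as maintenance either.
3. Label (A) and (B) as uncontrolled descriptive changes, and state that no untreated comparison exists after week 4.

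The cost is wording in the analysis plan and a reanalysis of data already being collected, with no new patients or visits. The downside is that maintenance may have to be reported as inconclusive: with the half-widths above, even an observed change of zero would exclude a 3-point loss only at r = 0.8. The randomised comparison estimates stopping against continuing. It cannot show that benefit over no treatment persists at week 8.
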